### Statistical analyses

The study results will undergo statistical analysis with SPSS software version 19.0. Comparisons between groups will be an analysis of covariance (ANCOVA) with treatment and baseline entered in the model. Estimate, 95% confidence intervals (CIs), and *p* values will be reported. The analysis population will adopt Intent to treat (ITT) and ignoring missing data.

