### Inclusion criteria

Patients with BC phases I–III, who have finished postoperative radiotherapy/chemotherapy within four months to two years will be included.

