### Blinding

After completing the baseline questionnaire and physical fitness tests, the participants will be enrolled and a computer-generated random list generated by SPSS 16.0 will be used for randomization. The random number list is kept strictly confidential by the Data Coordination Committee (DCC) staff. Eligible patients will be randomized to the experimental group or the control group at a 1:1 ratio. The group numbers will be provided in envelopes made from carbonless paper. The envelopes will be kept by a study administrator who will not directly participate in the recruitment or follow-up of any participant and the group numbers will be subsequently disclosed. Different people will enroll participants and assign participants to interventions.

The division results are kept by the study designer until the end of the study to ensure allocation concealment, which means the allocation is bound to both the result evaluator and the data analyzer. The participants and the treatment provider will be instructed not to disclose the allocation to the result evaluator.

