### Sample size

A total of 52 participants (26 in each group) completing follow-up will provide 90% power (α = 0.05) to detect 9.5 points [26] in SF-36 MCS assuming a standard deviation of 11.6 points [27]. Assuming a 15% drop-out rate between baseline and follow-up, 60 participants will be enrolled in the study.

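### Entry spans 4 to 24 months after treatment, and the primary ANCOVA leaves out time since treatment: the analysis is valid, but may give up precision that is cheap to recover

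*Protocol article*

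**What the plan says.** Four sections of the protocol article bear on this.

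- **Inclusion criteria:** "Patients with BC phases I–III, who have finished postoperative radiotherapy/chemotherapy within four months to two years will be included". The upper end of the window is six times the lower end.
- **Blinding:** "a computer-generated random list generated by SPSS 16.0 will be used for randomization", and "Eligible patients will be randomized to the experimental group or the control group at a 1:1 ratio". No stratification or minimisation factor is named.
- **Statistical analyses:** "Comparisons between groups will be an analysis of covariance (ANCOVA) with treatment and baseline entered in the model". The section does not define baseline; the natural reading is the baseline value of the outcome. Estimates, 95% confidence intervals and p values are to be reported.
- **Sample size:** 52 completers, 26 per arm, for 90% power at α = 0.05 to detect 9.5 points on the SF-36 MCS with an SD of 11.6. Enrolment is 60, to allow for 15% dropout.

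**The concern.** Baseline adjustment removes differences in the MCS level at entry. It does not necessarily remove differences in the change to be expected over the next 12 weeks. Two patients with the same baseline MCS, one 4 months and the other 24 months past treatment, may be at different points of recovery. Baseline MCS stands in for time since treatment only as far as the two are correlated.

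If time carries further prognostic information, leaving it out has two effects. The residual variance is larger than it need be. And in a trial whose arms happen to differ in time since treatment, part of that difference stays in the estimate. With about 52 completers, noticeable imbalances are not rare. The variable has to be known at least roughly for every patient, because eligibility depends on it.

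**Working it through.** **1. The plan's own sample size.** Inputs from the Sample size section: difference 9.5, SD 11.6, α = 0.05, power 90%. With n per arm = 2 × (11.6/9.5)² × (z_α + z_β)²:

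- one-sided α: 2 × 1.491 × (1.645 + 1.282)² = 25.5, so 26, the stated figure;
- two-sided α: 2 × 1.491 × (1.960 + 1.282)² = 31.3, so 32. With 26 per arm, a two-sided t-test has 82.5% power;
- two-sided ANCOVA with baseline–outcome correlation 0.42: 31.3 × (1 − 0.42²) = 25.8, so 26. The document states no correlation.

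The sidedness question is separate. It matters here only because the margin on power may be thin.

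**2. Validity of the planned model.** 20,000 trials were simulated per scenario with 26 per arm. Assumptions: baseline–outcome correlation 0.5, and time uniform over 4 to 24 months. The correlation of time with baseline was 0.3 (0 in the scenario with no association). With no treatment effect, ANCOVA on treatment and baseline gave:

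| Partial correlation of time with outcome, given baseline | Rejection rate |
|---|---|
| 0 | 4.8% |
| 0.2 | 5.0% |
| 0.3 | 4.9% |
| 0.5 | 5.2% |

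The mean estimate was within 0.04 points of zero, and the model SE of 2.80 agreed with the empirical SD of 2.78 to 2.83. There is no bias and no inflation over randomisations.

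**3. Precision and power at 9.5 points, two-sided.** The residual SD without time is 11.6 × √(1 − 0.5²) = 10.05. Adding time multiplies it by √(1 − r²), where r is the partial correlation. For k covariates and 52 patients, SE = residual SD × √[(2/26) × (1 + k/(49 − k))], with 49 residual degrees of freedom for k = 1 and 48 for k = 2. Without time, SE = 10.05 × √(0.0769 × 1.0208) = 2.82 and power is 91.1%.

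| r | SE with time (formula) | Power with time (formula) | Power without → with (simulated) |
|---|---|---|---|
| 0 | 2.84 | 90.5% | 91.0 → 90.4% |
| 0.2 | 2.79 | 91.6% | 91.2 → 91.8% |
| 0.3 | 2.71 | 92.9% | 90.9 → 92.9% |
| 0.5 | 2.46 | 96.5% | 91.1 → 96.6% |

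The two methods agree. The break-even value of r is about 0.15 (formula power 91.1% both ways). At a baseline correlation of 0.3, the same formula gives 85.2% without time, and 84.4, 85.8, 87.6 or 92.9% with it.

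**4. How large an imbalance can be.** For time uniform over 4 to 24 months, SD = 20/√12 = 5.77 months. The difference in arm means then has SE 5.77 × √(2/26) = 1.60 months, so 95% of trials fall within ±1.96 × 1.60 = ±3.1 months. In the 5% or so beyond that, the planned model's conditional false-positive rate was about 8, 10 or 19% at r = 0.2, 0.3 or 0.5. At r = 0 it was about 6%, which is simulation noise around 5%. These trials are already counted in the overall rates in step 2.

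**5. The same in points.** Assume 60 patients, 30 per arm, and call half of them early (an assumption). By the hypergeometric distribution, the arms differ by 6 or more early patients (20 percentage points) with probability 0.196, and by 8 or more with probability 0.070. With 18 early patients the probabilities are 0.158 and 0.047. If early patients gain 5 points more at the same baseline (an assumption), a 20-point imbalance shifts the estimate by 0.20 × 5 = 1.0 point. For 3 to 8 points the shift is 0.6 to 1.6, and if time does not predict change it is zero. One point is 1.0/2.8 = 0.36 of a standard error, in either direction.

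**The case against.** The strongest reply is that nothing here is an error. Treatment plus baseline is a standard and valid model. The randomised control group recovers naturally as well, and chance imbalance in any unmodelled variable is what the confidence interval and p value already allow for. Step 2 of the working bears this out, and that part of the objection stands in full.

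A reader might infer from the wide window that imbalance in natural recovery would be mistaken for an exercise effect. The documents do not support this. The error rate holds at 5%, an imbalance is as likely to hide a benefit as to mimic one, and no section says that time since treatment predicts MCS change.

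It is also fair that the gain is small unless the association is fairly strong, and that the 3 to 8 point recovery difference is assumed. A full protocol or analysis plan might name further covariates or a stratified list. Against that, the article does not leave the model open: it states which terms enter it. And a covariate is credible only if it is named in advance; adding one after an imbalance is seen would look data-driven.

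Finally, the items that the Data collection and management section lists as recorded do not include the date treatment ended. Its availability is inferred from the eligibility rule, so recording it has to be part of the fix.

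**Conclusion.** The point holds as a minor, optional improvement. The planned ANCOVA is unbiased over randomisations and keeps about 5% type I error. What it may lose is precision: about 0.5, 2 or 5 percentage points of power at partial correlations of 0.2, 0.3 or 0.5, with baseline correlation 0.5 and 26 per arm. It also leaves a conditional shift of around 1 point, about a tenth of the 9.5-point target, in a trial with a 20-point imbalance and a 5-point recovery difference. Both depend on an association that the document does not quantify, and both vanish if time is not prognostic given baseline.

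A reader might also extend the point to disease stage, since stages I to III are admitted. Nothing in the document or in this working supports a separate claim about stage.

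**What to change.** Before unblinding, amend the Statistical analyses section so that the primary ANCOVA contains treatment, baseline SF-36 MCS and months since the end of the last radiotherapy or chemotherapy. State the functional form in advance. A linear term is simplest, although it would capture only part of a curved recovery course. Add the end-of-treatment date to the report form if it is not there, and complete it from the medical record for patients already enrolled.

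Recruitment was under way at submission, so a covariate is simpler than changing the randomisation list. Eligibility, treatment and randomisation are untouched.

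The cost is one phrase in the analysis text, one data item, one of 49 residual degrees of freedom and, if time is not prognostic, under 1 percentage point of power.

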### Ethical approval and dissemination

This study follows the principles of the Declaration of Helsinki (Version Edinburgh 2000). Before participating in this research, every potential participant should be informed of the detailed study information, while participants can ask questions by phone, e-mail, and face to face. Only patients who sign the informed consent form will be included. This study has been approved by the Ethics Committee of the Second Hospital of Shandong University (KYLL-2017(KJ)P-0003). Personal information about potential and enrolled participants will be collected and stored separately from medical records and will be only accessible for the assessors who contact the participants for data assessment. In case of an unexpected serious adverse event (e.g. life-threatening event or permanent damage) over the course of the study, we will report the serious adverse event to the local Ethics Committee. The Ethics Committee and the study team will then decide in accordance, in the best interests of the patient, if the study procedures will be continued or terminated. The results of this study will be disseminated by presenting at international conferences and publication in peer-reviewed journals. Participants will learn about the results of the study.

The principal investigator is responsible for publication of the results of this study in whole or in part. Neither the complete nor any part of the results of the study carried out under this protocol, nor any of the information provided by the sponsor for the purposes of performing the study, will be published or passed on to any third party without the consent of the study sponsor. The study designer will have access to the final trial dataset. Any investigator involved with this study cannot access the trial data. Data sharing statement is as follows: no later than three years after the collection of the one-year post-randomization interviews, we will deliver a completely deidentified dataset to an appropriate data archive for sharing purposes.

## Discussion

There have been studies, both domestic and abroad, on physical exercise interventions with social media apps or smartphone apps in postoperative BC patients. However, as far as we know, the ways of intervention and measures of practice in these studies are relatively simple and few combined intervention studies have been conducted. Therefore, we propose this protocol of combined physical exercise intervention based on Internet and social media apps and plan to validate the feasibility and effectiveness of this protocol in BC rehabilitation via empirical research. If the expected results are achieved in this study, measures and methods of BC rehabilitation will be enriched. Meanwhile, it will also provide support for physical exercise interventions for other diseases, promoting the development of prevention and rehabilitation through physical exercise for patients with chronic diseases, who may also experience social and economic benefits as a result.

In this study, our objective is to perform a clinical trial with a relatively high standard of methods. The protocol of this trial, implementation, and reports will comply with the recommendations in Consolidate Standards of Reporting Trial (CONSORT). A Standard Protocol Items: Recommendations for Interventional Trials (SPIRIT) [28] diagram is provided in Additional file 1.

### Trial status

At the time of manuscript submission, recruitment for the study is underway but has not been completed.

## Abbreviations

BC: Breast cancer
CONSORT: Consolidated Standards of Reporting Trials
DCC: Data Coordination Committee
QOL: Quality of life
RPE: Rate of perceived exertion
SF-36: 36-item Short Form Health Survey
